#### Plans to promote participant retention and complete follow-up {18b}

##### Patient-directed strategy

Patients in the intervention group will be contacted by the practice via PIA-App, subsequently by phone, if no BP values are transmitted for several weeks.

##### Practice-directed strategy

Regular faxes by the institute ask for practices’ actual patient recruitment numbers and if any support is needed. The research team offers practice-specific support including practice visits regarding recruitment and use of the PIA-ICT. The institute will record all questions and support measures.

Discontinuing patients and the respective reasons are recorded by the practices; the research team records discontinuing practices and respective causes. All data available from discontinuing patients and/or practices will be analyzed.

##### Data management {19}

Data management will be carried out by the trial center according to standardized procedures as defined in the current standard operating procedures (SOPs). The data management system used by the trial center has an integrated audit trail and is Good Clinical Practice (GCP)-compliant. Data will be entered by appropriately trained data entry staff who are familiar with the study specifics. Double data entry will be used to ensure data quality for paper-based information. Data from the PIA-PrMC will be transmitted electronically to the study centers. Missing data will be addressed by imputation methods according to standard [60]. All personal data will be kept confidential in an access-restricted database. All analyses will be performed using pseudonymized data. The pseudonymized data will be stored at the ZKSE, University Hospital Essen, and the Institute of Family Medicine and General Practice, University of Bonn. The latter institute will manage the access to the data set.

##### Confidentiality {27}

Confidentiality issues and data protection issues are part of the ethics statement. The data protection agency of the University Hospital Bonn had agreed to the following approaches:
Confidentiality regarding patients’ and practices’ data

Contact data of practices and personnel involved are stored in access-restricted data files at the institute and the trial center. GPs’ and practice assistants’ questionnaire data will be managed as pseudonymized data files.

All personal information of patients will remain in the practices. The names of enrolled patients will be kept at the practices in a separate access-restricted paper file. The data analysis will be performed with pseudonymized data only to allow for maximum protection of participants. Information on potential participants which were not enrolled will remain solely in each practice. Before, during, and after the trial, all data will be stored in the institute and the trial center in access-restricted files according to their standard operating procedures.
2.Confidentiality in PIA-ICT (PIA-App and PIA-PrMC software)

The PIA-App will not store any personal data on the patient’s smart device. The regularly transmitted BP data does not contain any personal data. The communication between the PIA-App and the PIA-PrMC, i.e., data transfer and transmission, takes place via a secured server at the University Hospital Bonn. This communication and data transfer is encrypted by using https/Transport layer Security (TLS) with encryption algorithms on the elliptic curve and perfect forward secrecy (TLS negotiation BSI TR-021202-2). After the user (GP, practice assistant) logs on to the PIA-PrMC, a token is generated for encrypted communication with the PIA-App (Bearer Token). This token is transmitted with every communication.
3.Data transfer to trial center and the institute

Pseudonymized patient and practice data will be exported from the PIA-PrMC. This data is first stored on the GP’s practice computer. Exports will only contain pseudonymized data, i.e., personal data such as surname, name, and date of birth of the patients are removed prior to export. The export is a zip file with AES (Advanced Encryption Standard) password encryption. This file is transmitted electronically to the Institute for Family Medicine and General Practice as well as the trial center.

#### Plans for collection, laboratory evaluation, and storage of biological specimens for genetic or molecular analysis in this trial/future use {33}

Not applicable.

## Statistical methods

### Statistical methods for primary and secondary outcomes {20a}

Descriptive data will be used for all participant characteristics and scales as applicable (e.g., frequencies, means). Analyses of all scales will follow scale-specific recommendations. The confirmatory analysis for the primary endpoint is based on a generalized linear mixed models (GLMM) with a significance level of 5% (2-sided).

#### Primary endpoint

A GLMM is used because the primary endpoint is a patient-related outcome and these are embedded in the clusters. The model will include relevant patient covariates (e.g., age, gender). Taking the data’s cluster structure into account, the affiliation of patients to practice is included in the model as a random effect. The null hypothesis (no difference in BP control rate) will be rejected if the *p*-value for the Wald test statistics for the intervention effect is < 0.05. The *p*-value for the Wald test statistics for the intervention effect is < 0.05. The *p*-value for the Wald test statistics for the intervention effect is < 0.05. The adjusted odds ratio (OR) and the associated 95% confidence interval will be reported.

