#### Eligibility criteria on patient level

All of the following inclusion criteria apply: (a) age 40 to 79 years, (b) diagnosed with essential hypertension (ICD I10), (c) resting practice BP > 140/90 mmHg (calculated as the mean value of the 2nd and 3rd BP readings obtained by trained personnel), (d) need or use at least ≥ 1 antihypertensive substance (drug), (e) insured by the statutory health insurance, (f) equipped with smart devices (tablet or smartphone with android 6 or higher), (g) sufficient skills to use the smartphone or tablet (defined as device use at least 3 times a week), and (h) has sufficient language skills to understand the study documents.

The exclusion criteria are as follows: (a) known white coat hypertension, (b) critical health conditions at the time of inclusion (e.g., hypertensive crisis, BP-related symptoms such as dizziness or headache), (c) chronic renal failure requiring dialysis, (d) being pregnant or breastfeeding, (e) hyperkalemia, (f) secondary hypertension (e.g., renal artery stenosis), and (g) heart failure NYHA III or IV.

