#### Sample size {14}

The sample size was calculated based on the primary outcome. Using data from the study of Margolis et al. [9], we assumed a BP control rate of 65% in the intervention group and 50% in the control group after 12 months. The sample size calculation was performed in PASS V14, using an unpooled 2-sided *Z*-test to compare two proportions in a cluster-randomized design. Assuming that both study arms comprise the same number of clusters (practices), the inter-cluster coefficient is 0.055 [14] and the mean cluster size is 15 patients, 2 × 405 = 810 patients (27 clusters per study arm) are required to detect a group difference of 15% (65% vs 50%) with a power of 90%. Although the case number calculation is based on a 2-sided *Z*-test with an unpooled variance in a cluster-randomized setting, there is sufficient power for the calculation of generalized linear mixed models (GLMM) with additional covariates. Assuming a case number of 810 patients and incidence rates of cardiovascular events between 2 and 5% [3], it is a probability of 100% to observe at least one such event (PASS V14). Based on experience from a previous CRT on hypertension management by GP [15], a 10% drop-out rate in the practices is assumed; therefore, 3 more practices are recruited per study arm. Therefore, the study aims for a cluster-randomized trial with 60 GP practices (30 intervention, 30 control) with one physician, two practice assistants, and 17 patients each (total 1020 patients).

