### Assignment of interventions: allocation

#### Sequence generation {16a}

The randomization is conducted by the independent trial center responsible for data management and monitoring. The allocation sequence is computer-generated based on random numbers. Stratified block randomization (1:1) is used to ensure a balanced distribution of urban and rural localized practices in the intervention and control arm.

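### The primary model as written omits the urban/rural randomisation stratum and does not commit to baseline blood pressure, although the trial holds both

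*Protocol article*

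**What the plan says.** The Primary endpoint section of the protocol article sets out a GLMM for the control rate. On covariates it says: "The model will include relevant patient covariates (e.g., age, gender"). On clustering it says: "the affiliation of patients to practice is included in the model as a random effect". The null hypothesis is tested by a Wald test of the intervention effect, "with a significance level of 5% (2-sided"), and the section adds: "The adjusted odds ratio (OR) and the associated 95% confidence interval will be reported".

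Two variables that bear on this model are described elsewhere. Under Sequence generation {16a}: "Stratified block randomization (1:1) is used to ensure a balanced distribution of urban and rural localized practices in the intervention and control arm". Under Eligibility criteria on patient level, resting practice pressure must exceed 140/90 mmHg, "calculated as the mean value of the 2nd and 3rd BP readings obtained by trained personnel". The primary outcome is built from the same kind of reading and judged against the same 140/90 threshold. Neither the stratum nor baseline pressure is named in the statistical sections {20a} to {20c}.

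**The concern.** A factor that restricts the randomisation would normally appear in the analysis. Here the stated class of covariates is patient-level and the stratum is a property of the practice, so the model as described does not match the allocation scheme. If location predicts control, the between-practice variance that stratification balanced stays in the standard error.

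Baseline pressure raises a second issue. A patient who enters just above 140 mmHg is likelier to finish at or below it than one who enters far above, so baseline pressure should be a leading predictor of the endpoint. Age and gender are weaker examples to give.

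The design makes this more than a precision question. Practices are randomised after the GP consents and are told their allocation (Recruitment {15}, Implementation {16c}). Their staff then screen and enrol patients, and practice personnel cannot be blinded ({17a}). Randomising practices does not by itself protect the mix of patients enrolled afterwards. Precision is also scarcer than first planned, since target power was lowered from 0.9 to 0.8.

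**Working it through.** **1. The plan's own sample size.** Inputs from Sample size {14}: "we assumed a BP control rate of 65% in the intervention group and 50% in the control group after 12 months"; "the inter-cluster coefficient is 0.055 [14] and the mean cluster size is 15 patients"; two-sided 5% level; unpooled Z-test.

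- Design effect: 1 + (15 − 1) × 0.055 = 1.77.
- Variance term: 0.65 × 0.35 + 0.50 × 0.50 = 0.4775.
- 90% power: (1.960 + 1.282)² × 0.4775 / 0.15² = 222.99 per arm. Times 1.77 this is 394.7, or 26.3 clusters, so 27 clusters and 405 patients per arm. This matches.
- 80% power: (1.960 + 0.842)² × 0.4775 / 0.15² = 166.57 per arm. Times 1.77 this is 294.8, or 19.7 clusters, so 20 clusters and 300 patients per arm. This matches, and power at 20 × 15 is 0.807.
- Dropout: 20/0.9 rounds up to 23 practices per arm, 15/0.9 rounds up to 17 patients, and 46 × 17 = 782. This matches.

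The calculation assumes no covariate adjustment, so the covariate list does not make it wrong.

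**2. How large a chance imbalance in baseline pressure could be.** The documents give no spread for baseline pressure. Assumptions: SD of baseline systolic pressure 10 mmHg (truncated above 140), the protocol's ICC of 0.055 applied to it, and 300 patients per arm.

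- SE of the difference between arms: 10 × √(2 × 1.77/300) = 1.09 mmHg.
- 95% limit: 1.96 × 1.09 = 2.1 mmHg.
- With an ICC of 0.10 the design effect is 1 + 14 × 0.10 = 2.4. The SE is then 10 × √(2 × 2.4/300) = 1.26 mmHg and the limit about 2.5 mmHg.

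**3. What that imbalance does to the control rate.** Further assumptions: slope of follow-up on baseline 0.3 to 0.5, follow-up SD 15 mmHg, and a control rate near 50%, where the standard normal density is about 0.4. The shift is imbalance × slope / 15 × 0.4.

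- Slope 0.3: 2.1 × 0.3/15 × 0.4 = 0.017.
- Slope 0.5: 2.1 × 0.5/15 × 0.4 = 0.028.

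This is about 1.7 to 2.8 points. A large-sample simulation with the same slopes gave 2.5 to 3.9 points for 3 mmHg and 4.1 to 6.4 points for 5 mmHg, which agrees per mmHg.

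**4. Precision.** Clustered data were simulated with 20 practices of 15 patients per arm and analysed by logistic GEE with exchangeable correlation, as a stand-in for the GLMM (350 to 400 runs per setting; Monte Carlo error about 2 points per power). The assumed latent correlation of baseline pressure with the outcome runs from 0.2 to 0.6. The assumed stratum share of the between-practice variance runs from none to about half.

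| Correlation | Stratum share | Neither | Baseline only | Stratum only | Both |
|---|---|---|---|---|---|
| 0.2 | none | 0.808 | 0.812 | 0.818 | 0.822 |
| 0.2 | about a quarter | 0.855 | 0.862 | 0.885 | 0.892 |
| 0.2 | about half | 0.838 | 0.840 | 0.885 | 0.905 |
| 0.4 | none | 0.829 | 0.860 | 0.834 | 0.869 |
| 0.4 | about half | 0.834 | 0.849 | 0.886 | 0.914 |
| 0.6 | none | 0.771 | 0.826 | 0.777 | 0.834 |

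Adding both gains 1.4 to 8.0 points. The setting with correlation 0.6 and a strong stratum effect was not completed. Where the stratum has no effect, adding it still shows 0.5 to 1.0 points, so gains of that size should not be read as real.

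**5. Scale of the odds ratio.** In the settings without a stratum effect, the log odds ratio was 0.610 to 0.628 with no covariates (odds ratio about 1.85). With baseline pressure it was 0.629, 0.692 and 0.781 for correlations 0.2, 0.4 and 0.6, that is, odds ratios of about 1.9, 2.0 and 2.2.

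**The case against.** The strongest reply is that age and gender are only examples. Baseline pressure is a patient covariate, is plainly relevant, and can be included without departing from the text. A full covariate list is ordinary content for a statistical analysis plan, and that plan is not shown. This stands: a reader might infer that baseline pressure is excluded, and the protocol does not say so. For the same reason, the open list and the absence of a statement that analysts are blinded are not counted as faults. A plan not shown may settle both, and section {17a} commits analysts to predefined procedures. The reply does not reach the stratum, because the stated class is patient covariates and urban/rural location is not one.

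A reader might also infer that baseline imbalance threatens a large part of the effect. Gaps of 3 to 5 mmHg would move the control rate by 2.5 to 6.4 points, or 17% to 43% of the 15-point target. Chance does not plausibly produce such gaps: 3/1.09 = 2.8 and 5/1.09 = 4.6 standard errors, and 3 mmHg is still 2.4 standard errors at an ICC of 0.10. They would need selective recruitment. The design leaves room for that but the documents do not show it, and section {15} asks practices to list and screen all their hypertensive patients. Adjustment would in any case not remove selection on unmeasured factors.

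Finally, the precision cost of omitting the stratum depends on location being prognostic, and the documents give no such effect. The gain may be nil.

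**Conclusion.** The point holds in a limited form. The primary model as written does not carry the randomisation stratum and does not commit to baseline practice pressure.

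Omitting the stratum leaves the comparison unbiased and usually makes the test somewhat conservative. Omitting baseline pressure gives up precision and leaves the result exposed to imbalance in the severity that largely decides the endpoint. By chance alone that exposure is about 2 mmHg at the 95% limit, or roughly 2 to 3 points of control rate, and more only if recruitment differs between arms. The power gain from both variables is about 1 to 8 points and is indicative only.

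These sizes rest on an assumed baseline SD of 10, follow-up SD of 15, slopes of 0.3 to 0.5, the protocol's ICC carried over to baseline pressure, and GEE in place of the GLMM. The sample size reproduces and is unaffected. This is an improvement worth making, not an error that invalidates the analysis.

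**What to change.** Specify the primary model as a logistic GLMM with these fixed effects: arm, baseline systolic and baseline diastolic practice pressure (both continuous), urban/rural stratum, age and gender. Practice enters as a random intercept. Use the same covariates in the models for the systolic and diastolic outcomes.

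The cost is one sentence and no new data. The model is not overloaded: at 2 × 300 patients the planned rates give 0.65 × 300 + 0.50 × 300 = 345 controlled and 255 uncontrolled patients for six fixed-effect terms. The one downside is that the conditional odds ratio changes in scale once baseline pressure enters (about 1.85 to between 1.9 and 2.2 in the simulations). A standardised risk difference should therefore be reported beside it; this also allows direct comparison with the 15-point planning difference.

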#### Secondary endpoints

All secondary analyses will be performed exploratively, i.e., without adjustment, using GLMM and adequate statistical standard procedures, taking into account the cluster structure of the data. A significance level of 5% will be assumed for all statistical analyses. Under individual randomization, an OR of 1.5 could be detected with 2 × 405 patients and a power of 80% and an OR of 1.6 with a power of 90% (Fisher’s exact test; PASS V14). We expect similar, probably slightly higher ORs for this CRT design.

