##### Changes required due to the SARS-CoV-2 pandemic

The scheduled recruitment period was influenced by the pandemic, which led to more SARS-CoV-2-related workloads and perceived insecurities on behalf of practices as well as fewer practice visits by patients due to social distancing and lockdown regulations. Accounting for this unexpected interference, the scheduled recruitment period for both practices and patients needed to be prolonged. To support recruitment, statutory health insurances involved in the project applied several patient information strategies. In addition, given an overall limited project time, the target number of patients was reduced based on a re-calculation of the sample size by the evaluator assuming a power reduction from 0.9 to 0.8 (with all other parameters kept identical) resulting in a target patient number of 2 × 300 = 600 patients (20 clusters per study arm) to detect a group difference of 15% (65% vs 50%). Assuming a 10% drop-out rate for practices and a 10% dropout rate for patients, three more practices and 2 more patients in each practice will be recruited. In summary, this cluster-randomized trial will be conducted with 46 GP practices (23 intervention, 23 control) with one GP, two practice assistants, and a mean of 17 patients each (total 782 patients). In addition, the minimum duration of the intervention was reduced to at least 6 months. This is justified by international studies of ICT delegation models which showed significant improvements in hypertension control already after this shorter period [9, 16, 17].

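### The detectable odds ratios for secondary outcomes are carried over to the cluster design without a design effect and were not restated for the reduced target of 2 × 300.

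*Protocol article*

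**What the plan says.** Under Secondary endpoints the protocol article makes a sensitivity statement in three parts:

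- "Under individual randomization, an OR of 1.5 could be detected with 2 × 405 patients and a power of 80" per cent;
- "an OR of 1.6 with a power of 90% (Fisher’s exact test; PASS V14");
- for the trial as designed, "We expect similar, probably slightly higher ORs for this CRT design".

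The same section says that the secondary analyses are exploratory and are done "taking into account the cluster structure of the data". It adds: "A significance level of 5% will be assumed for all statistical analyses". The opening of the statistical methods section makes the level two-sided for the primary analysis.

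Two other places bear on this. Sample size {14} states, for the primary outcome, that "the inter-cluster coefficient is 0.055 [14] and the mean cluster size is 15 patients". The subsection on pandemic changes then lowers the power from 0.9 to 0.8 with the other inputs unchanged, "resulting in a target patient number of 2 × 300 = 600 patients (20 clusters per study arm").

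**The concern.** The planned secondary analyses allow for clustering, so they pay for it in precision. The sentence on the cluster design acknowledges the direction of that loss but calls it slight. No ICC, cluster size or design effect is attached to it. The one ICC in the protocol implies a loss that is not slight. The sample size in the statement is also the one that the pandemic section replaced.

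A reader who takes the sentence at its word would think that the trial has 80% to 90% power for odds ratios a little above 1.5 to 1.6. That reader could then give a null secondary result more weight than the design supports. No sample size, decision rule or confirmatory claim rests on these figures.

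**Working it through.** **Inputs**

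- Test and level: Fisher's exact test (Secondary endpoints), 5%, taken as two-sided as for the primary analysis.
- Patients per arm: 405 (original) and 300 (reduced).
- ICC 0.055 and mean cluster size 15 (Sample size {14}, given for the primary outcome).
- Control rate for a secondary outcome: not stated. Assumed 50%; the effect of other rates is shown below.
- ICC for secondary outcomes: not stated. 0.055 is used first, then a range.

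**Step 1. Reproduce the stated figures.** An odds ratio OR applied to control rate p gives the intervention rate p·OR / (1 − p + p·OR). At p = 0.5 this is 1.5/2.5 = 0.600 for OR 1.5 and 1.6/2.6 = 0.615 for OR 1.6. Exact Fisher power with 405 per arm, by full enumeration, is 0.803 and 0.903. At p = 0.4 it is 0.803 and 0.906. The stated 1.5 and 1.6 therefore hold for individual randomisation at control rates of about 40% to 50%. They do not hold at every rate: at p = 0.2 the powers are 0.657 and 0.793.

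**Step 2. Design effect.** 1 + (15 − 1) × 0.055 = 1.77. The protocol's primary calculation is consistent with this value. The unpooled Z formula for 65% vs 50% needs 223.0 per arm at 90% power. Then 223.0 × 1.77 = 394.7, which rounds up to 27 clusters of 15 = 405. At 80% power, 166.6 × 1.77 = 294.8, which rounds up to 20 clusters = 300.

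**Step 3. Effective sample size.** 405 / 1.77 = 229 per arm; 300 / 1.77 = 169 per arm.

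**Step 4. Detectable odds ratios and power (control rate 50%, Fisher's exact test)**

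| Patients | ICC | Effective n per arm | OR at 80% power | OR at 90% power | Power for OR 1.5 | Power for OR 1.6 |
|---|---|---|---|---|---|---|
| 2 × 405 | 0 | 405 | 1.50 | 1.60 | 80% | 90% |
| 2 × 405 | 0.055 | 229 | 1.72 | 1.88 | 55% | 68% |
| 2 × 300 | 0 | 300 | 1.60 | 1.73 | 68% | 80% |
| 2 × 300 | 0.055 | 169 | 1.89 | 2.10 | 43% | 54% |

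On the log scale at 80% power, the detectable effect grows by a factor ln 1.72 / ln 1.50 = 1.34 at 2 × 405 and ln 1.89 / ln 1.50 = 1.57 at 2 × 300.

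**Step 5. How much depends on the ICC.** Detectable ORs at 80% / 90% power, control rate 50%, assumed ICCs:

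- 2 × 405: ICC 0.005 gives 1.52 / 1.62; 0.01 gives 1.54 / 1.65; 0.02 gives 1.59 / 1.71.
- 2 × 300: ICC 0.01 (design effect 1.14, effective n 263) gives 1.67 / 1.81.

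**Step 6. How much depends on the control rate.** With ICC 0.055 and 2 × 300, a continuity-corrected approximation gives 1.89 to 2.15 (80%) and 2.08 to 2.46 (90%) over control rates of 20% to 70%. At a 10% control rate, exact Fisher gives 2.46 and 2.76.

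**The case against.** The strongest reply is that ICC 0.055 belongs to the primary outcome and the protocol never assigns it to a secondary one. This stands. With an ICC of about 0.01 or less and 2 × 405 patients, the sentence is a fair description. The size of the shortfall is therefore conditional.

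A reader might go further and infer that the primary sample size calculation contradicts the sentence: it needs 2 × 405 for 90% power at 65% vs 50%, an odds ratio of 0.65/0.35 = 1.86, whereas the sentence suggests something near 1.6. The documents do not support that reading. The primary calculation concerns another outcome, uses an unpooled Z-test and has its own assumed ICC. It shows that the sentence is optimistic if secondary outcomes cluster like blood pressure control, and no more than that.

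It is also fair to say that the protocol labels 1.5 and 1.6 as individual-randomisation figures, names the 2 × 405 sample and gets the direction right. The article describes the original plan first and reports pandemic changes in separate subsections, so the 2 × 405 is stale text and not an arithmetic error. However, the statement is the only one on sensitivity for secondary outcomes, and it describes a sample that the trial no longer aims for.

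Finally, the analyses are exploratory, and many secondary outcomes (blood pressure change, scale scores, counts, time to control) are not naturally summarised by an odds ratio from a two-by-two table. Nothing in the protocol says that null results will be taken to exclude odds ratios of 1.5 to 1.6. This limits the severity but does not make the sentence right.

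**Conclusion.** The point holds in conditional form. The 1.5 and 1.6 are correct as labelled; their extension to the cluster trial is not supported by any stated input. On the only ICC and cluster size that the protocol gives, and an assumed 50% control rate, the current target of 2 × 300 detects odds ratios of about 1.9 (80% power) and 2.1 (90% power). An odds ratio of 1.5 would then have 43% power, not about 80%.

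The conclusion about the current sample does not rest on that ICC. With no clustering at all, 2 × 300 already needs 1.60 and 1.73. How far above that the true figures lie depends on ICCs and base rates that the protocol does not state for secondary outcomes. Severity is minor.

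**What to change.** Replace the sentence that extends the odds ratios to the cluster design with:

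> For binary secondary outcomes with 2 × 300 patients, mean cluster size 15 and a 50% control rate, ORs of about 1.9 (80% power) and 2.1 (90% power) are detectable if the ICC assumed for the primary outcome (0.055) applies, and about 1.7 and 1.8 if the ICC is 0.01. Larger ORs are needed at low base rates (about 2.5 and 2.8 at 10% with ICC 0.055).

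The individual-randomisation figures may stay if they are labelled as the original 2 × 405 reference, with the control rate behind them stated. The cost is a text change only, with no effect on conduct, recruitment or the primary analysis. The stated detectable effects become less favourable.
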